#### Stimulation procedures

HD-tDCS will be delivered to all experimental groups with a Starstim-8® device, a wireless hybrid EEG/tES 8-channel system (Neuroelectrics, Barcelona, Spain). The Neuroelectrics Instrument Controller® software (NIC) associated with this hardware will be used to pre-program all HD-tDCS and EEG protocols and carry out interventions. Given the four-parallel arms of our study design (ipsi-DLPFC, contra-CEREB, ipsi-DLPFC + contra-CEREB, and SHAM) and considering participants with left or right hemisphere stroke, a total of 8 HD-tDCS protocols will be pre-programmed.

During stimulation sessions, participants will wear a neoprene cap adapted to the circumference of their head ensuring correct placement for NG pistim® electrodes (πcm^2^ surface, Ag/AgCl) embedded in SignaGel® (Parker laboratories, USA) to keep impedances below 10 KΩ. Every participant will receive 10sessions of tDCS, 20 min each and 5 daily sessions per week (Monday to Friday) during 2 consecutive weeks (W1 and W2 of participants’ schedule).

The tDCS device integrates a maximum of 8 electrodes to deliver stimulation. However, note that depending on the experimental tDCS group, different electrodes will be actively involved in stimulation at each condition (see tDCS montage protocol section). To conceal the stimulation condition and preserve the blinding of the operator and the participant, all 8 available electrodes will always be positioned on the participant’s head cap and will have their impedance tested. Crucial values such as mean voltage, current intensity, and impedance of the different electrodes employed will be recorded automatically during the sessions. Targeted regions are represented in Figs. 2 and 3.

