#### Screening of hemispatial neglect

In order to monitor the presence of hemispatial neglect, participants will conduct a letter cancellation test, a Bells cancellation test, and a line bisection test. The letter cancellation test quantifies the presence of visuo-spatial  neglect and visual search/scanning deficits [56]. In the task, a total of *n* letters is distributed into 6 lines presented in paper format. Among them, the letter “H” is repeated 104 times. Participants will be asked to visually screen the paper sheet and find and outline as many letters “H” as they can find. The Bells cancellation test quantifies visual neglect deficits in the extra personal space [57]. A total of 35 bells are embedded within 280 distractors presented in paper format. Participants will be instructed to circle or cancel off all drawings corresponding to bells. All stimuli are of the same size and displayed in black color over a white background. Though they might appear randomly distributed, bells are presented in 7 columns; 3 columns on the left and the right hemifields and one in the middle, with 5 bells and 40 distractors on each one. The sheet of paper with the test display will be placed right in the middle of the visual field and the participant is free to explore the document with his/her gaze. Finally, the line bisection test identifies and quantifies visuo-spatial orienting impairments and spatial neglect deficits [58]. In this task, several examples of two types of black lines, 5 and 10 cm long, are presented on a white paper sheet placed in the middle of the participant’s visual field. Participants, who are free to explore stimuli with their  gaze, are instructed to identify the center of each horizontal line and bisect it with a pencil.

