In order to quantify sustained attentional abilities (as a proxy of dorsolateral prefrontal  modulation by tDCS) with the AX-CPT task, we will analyse the total number of errors used as a proxy of sustained attention failure. An ordinal value will be taken and group means will be compared between pre- vs. post-tDCS  and for the follow-up milestone. In order to indentify and quantify changes of visuo-spatial performance (as a proxy of visuo-spatial orienting and selective attentional disability), the number of  crossed/circled letters (letter cancellation test) or bells (Bells cancellation test) and the shift (in mm and % of the total line length) of manual bisections from the precise midpoint of each line (line bisection test) will be analysed. Mean group total ordinal scores will be compared between groups acrossthe different time points (pre-, post-tDCS s and follow-up milestones). Other unanticipated complementary metrics could also be taken into account for the final analyses.

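### The hemispatial neglect tests are scored as total counts and a midpoint shift with no lesion-side coding, in arms that mix left and right strokes, so laterality is lost (minor, secondary outcomes)

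*Protocol article*

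**What the plan says.** The section on screening of hemispatial neglect gives the purpose: "In order to monitor the presence of hemispatial neglect, participants will conduct a letter cancellation test, a Bells cancellation test, and a line bisection test". It adds that "the line bisection test identifies and quantifies visuo-spatial orienting impairments and spatial neglect deficits". It also describes a Bells sheet with a left/right structure: "bells are presented in 7 columns; 3 columns on the left and the right hemifields and one in the middle", with five bells in each column. Line bisection uses lines of 5 cm and 10 cm.

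The section on analysis of clinical and cognitive performance outcome measures fixes the scores. They are the number of "crossed/circled letters (letter cancellation test) or bells (Bells cancellation test) and the shift (in mm and % of the total line length"), the shift being that of each manual bisection from the true midpoint. The scores are described "as a proxy of visuo-spatial orienting and selective attentional disability". The comparison is then stated: "Mean group total ordinal scores will be compared between groups", over the pre-treatment, post-treatment and follow-up visits.

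Three other sections matter:
- Stimulation procedures shows that both lesion sides are expected in every arm: "considering participants with left or right hemisphere stroke, a total of 8 HD-tDCS protocols will be pre-programmed".
- Randomization and blinding lists sex, age and stroke type as minimisation factors. Lesion side is not among them.
- Sociodemographic data lists the affected hemisphere among the stroke features recorded at baseline.

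**The concern.** Hemispatial neglect is a deficit of one side of space. A score for it should say on which side targets are missed, or in which direction the midpoint is displaced, relative to the lesion. The planned scores do neither. A total count treats omissions on the neglected side and omissions anywhere else as the same. A midpoint shift without a stated sign or reference to the lesion is ambiguous, and neither of its two plain readings suits an arm that mixes left and right strokes.

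At stake is the interpretation of a secondary comparison. A change in the cancellation totals could not be read as a change in neglect rather than in general search or attention. If the bisection shift were averaged with a raw left/right sign, a real reduction in bias could go largely unseen, and a chance difference between arms in lesion side could look like a baseline difference between arms.

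**Working it through.** The protocol gives no effect size, SD or power for these tests, so there is no figure of its own to reproduce. Its counts are consistent: 7 columns × 5 bells = 35; 4 arms × 2 lesion sides = 8 stimulation protocols; 4 × 15 = 60 patients.

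**Bells cancellation.** The layout is 15 left, 5 middle and 15 right bells. Take 14 omissions (assumed), placed in three ways:

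| Pattern | Omissions left / middle / right | Total found | Found right minus left |
|---|---|---|---|
| Left neglect | 12 / 2 / 0 | 35 − 14 = 21 | 15 − 3 = 12 |
| Right neglect | 0 / 2 / 12 | 21 | 3 − 15 = −12 |
| No side bias | 6 / 2 / 6 | 21 | 9 − 9 = 0 |

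The planned total is 21 in all three cases. An arm mixing left and right neglect also averages (21 + 21)/2 = 21, so opposite sides do not cancel in the total; only the side information is lost. A raw right-minus-left score would average (12 − 12)/2 = 0. Coded as ipsilesional minus contralesional targets found, with neglect on the side opposite the lesion, it is 12 for both neglect patterns and 0 for the unlateralised one.

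**Line bisection.** Let *b* be the bias towards the lesioned side and *p* the share of right-hemisphere strokes. None of the following values is in the documents: *b* = 5 mm, SD 4 mm, and a treatment that halves the bias in one arm.

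*Coded to the lesion side.* The contrast is 0.5 × 5 = 2.5 mm whatever *p* is. With 15 per arm and SD 4 mm, power is about 0.40.

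*Raw left/right sign.* The arm mean is *b*(2*p* − 1), so the contrast is 2.5 × |2*p* − 1|:
- *p* = 0.5: 0 mm (nothing retained)
- *p* = 0.4 or 0.6: 0.5 mm (20%)
- *p* = 0.3 or 0.7: 1.0 mm (40%)
- *p* = 0.8: 1.5 mm (60%)

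Chance imbalance in lesion side adds noise between arms. At *p* = 0.5, with simple chance allocation by side, the baseline difference between two arms of 15 has SD 2*b* × √(2 × 0.25/15) = 0.37*b*, or 1.8 mm at *b* = 5.

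*Unsigned shift.* A patient with no bias still scores on average 4 × √(2/π) = 4 × 0.798 = 3.2 mm. The mean of an absolute normal value is SD × √(2/π) × exp(−*b*²/(2 SD²)) + *b* × [1 − 2Φ(−*b*/SD)]. This gives 5.4 mm at *b* = 5 and 3.8 mm at *b* = 2.5. The contrast is about 1.6 mm, or 64% of the 2.5 mm from the lesion-coded score. The loss is milder than under the raw sign at these mixes, but direction is gone.

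**Millimetres and percentages.** The same proportional bias gives twice the millimetres on a 10-cm line as on a 5-cm line. A millimetre score pooled over both lengths would mix scales; the percentage score, also planned, does not.

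**The case against.** A reader might infer that opposite-side biases cancel in all three tests and that the scores therefore do not measure neglect. The documents do not support that. Omissions on either side lower a cancellation count, so a real reduction in neglect raises the mean total whatever the mix of lesion sides. The counts are sensitive to neglect; what they lack is specificity. The analysis section also names a broader construct, and a total fits it reasonably well.

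For line bisection, cancelling depends on a raw left/right sign that the article does not state. A full protocol or analysis plan, not shown here, may already use an absolute or lesion-coded shift. That stands, so the bisection point is a conditional one.

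Other objections also stand in part. Percentage of line length is already planned, and nothing says that millimetres are pooled over both line lengths. These are not the only relevant measures: the NIHSS covers hemineglect and the MoCA covers visuo-spatial function. Comparing post-treatment with baseline scores largely removes a fixed baseline offset between arms. Neglect is not an inclusion criterion, so many patients may show little bias and the illustration may not be typical.

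What survives is that the cancellation score is stated explicitly as a total, so for those two tests the loss of side is fixed in the text. Elsewhere the protocol does refer to lesion side: the montages are mirrored, and intra-hemispheric EEG connectivity is defined on the ipsilesional side. The allowance for further unanticipated metrics does not help, because a laterality score chosen after seeing the data would be post hoc.

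**Conclusion.** The point holds as a minor one on secondary outcomes. The tests are given to monitor a lateralised deficit, but the stated cancellation scores cannot separate it from a general search deficit: 21 of 35 in either case in the example. This follows from the sheet layout and the stated metric, and only the number and placement of omissions are assumed.

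The bisection score needs a stated sign. If it were a raw left/right value, the effect would vanish at an even mix of lesion sides and shrink to 20% to 60% at mixes from 60/40 to 80/20. Those percentages depend only on the mix and on equal, mirror-image bias on the two sides; the millimetre and power figures rest on the assumed bias and SD. Even lesion-coded, the test has modest power at 15 per arm under those values, so the gain is mainly in what the score means. Nothing here touches the primary FMA-UE analysis.

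**What to change.** In the section on analysis of clinical and cognitive performance outcome measures:

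1. Score line bisection as signed percentage of line length, positive towards the lesioned side, using the affected hemisphere recorded at baseline. Use this in place of any millimetre score pooled over 5-cm and 10-cm lines.
2. Add a side-difference score for each cancellation test: ipsilesional minus contralesional targets found. For bells, use the three left and three right columns and leave out the middle one. For letters, where no columns are described, split the sheet at its midline.
3. Keep the totals, labelled as a general visuo-spatial and attention score.

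The cost is rescoring of existing sheets, one extra score for each cancellation test, and a few lines of text. No new test, visit or variable is needed. Trial status reports 11 participants already completed; their side scores can be recovered if the marked sheets were kept. The rule should be written down before the data are analysed.

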### EEG data analysis

EEG data will be preprocessed using a hierarchically organized pipeline proceeding as follows [59]. Data will be first segmented into contiguous epochs after a preliminary investigation on which epoch length is the most robust for analyses. Then, a 2nd-order infinite Butterworth forward and backward filter with a 0.5–45 Hz low-pass high-pass filter at a resolution of 2 Hz (500 ms time windows) with a Hanning taper window will be applied. Eye movements or muscle-related artifacts will be removed using a common Independent Component Analysis (ICA), supervised and manually corrected after expert visual verification. Epochs with signals exceeding 120μv peak-to-peak amplitude will be also removed. Finally, channels will be re-referenced to their common average. Once data pre-processing is completed, (i) power spectrum density (PSD), (ii) connectivity, and (iii) complexity measures will be calculated. These approaches will be individually conducted on each subject for every condition or task (resting-state recordings, visuo-motor adaptation task, AX-CPT task, associated to everytime point of our study timeline (baseline, post-tDCS, follow-up).

 A time-frequency analysis will be conducted in order to explore pre tDCS (baseline) vs. post  tDCS and vs. follow-up tDCS-related modulations of patients’ oscillatory activity. To this end, the amplitude of the power spectrum density ($$\mu {V}^{2}$$) for each frequency band (δ: 0.5–4 Hz; θ: 4–8 Hz; α: 8–12 Hz; β: 12–30 Hz; γ: 30–60 Hz) will be computed by means of a Fast Fourier Transformation (FFT) using Welch’s method with a 500-ms periodogram. Relative and absolute spectral normalized power (NP) will be then extracted for each EEG electrode. Normalized average power for all frequency bands will be computed and plotted to explore differences between pre-tDCS (baseline) vs. post-tDCS and vs. follow-up milestones within each group and to compare differencesacross independent groups stimulated with different tDCS approaches.

Functional connectivity analyses by means of EEG sensor level coherence measures will be conducted to explore the “reshaping” of intra-hemispheric and inter-hemispheric connectivity (assessing functional integration and segregation mechanisms at the network level) by tDCS approaches. Given that resting-state data can be influenced by false positive correlations and to avoid the impact of volume conduction on raw coherence measures, we will compute more specifically the imaginary part of coherence (ImCoh) [60] by means of a Fast Fourier Transformation (FFT). Intra-hemispheric functional connectivity analysis will focus on synchronization measures between ipsilesional DLPFC and M1/premotor (electrodes and F3-C3/F4-C4) and also ipsilesional DLPFC and parietal systems (electrodes F3-P3/F4-P4). For inter-hemispheric functional connectivity, our analyses will focus on synchronization measures between premotor/M1 (electrodes C3–C4) and also prefrontal systems (electrodes F3–F4). Overall, an 8 × 8 connectivity matrix contemplating all connections between all possible electrode combinations, will be explored.

Complexity analyses will explore tDCS-related changes of neuroplastic properties and estimate the predictability of EEG signals following a given tDCS condition by calculating multiscale sample entropy (MSE). This estimate quantifies the probability that neighboring data points may be in a predetermined range in a time series $$\{{x}_{1}, {x}_{2},...{x}_{N}\}$$, computing how often patterns re-occur in a time-domain sample (i.e., temporal irregularity prediction in the time-domain). The computation of MSE is divided into two steps: (1) first, a moving-averaging procedure is computed to express the dynamic representation of a system; (2) Second, the degree of predictability is measured for each of the moving-averaged time series $${z}^{r}$$ by means of the sample entropy ($${Sample}_{En})$$ method (see [61] for a complete formulation of MSE).

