#### EEG acquisition

EEG data will be recorded with the same HD-tDCS equipment used for stimulation, a Starstim® 8 channel device controlled by the Neuroelectrics Instrument Controller® software (Neuroelectrics, Barcelona, Spain) able to sample scalp EEG signals at a frequency of 500 Hz using scalp NG pistim® electrodes ($${\mathrm{\pi cm}}^{2}$$ Ag/AgCl) and SignaGel® (Parker laboratories, USA). Skin/electrode impedance values will be automatically monitored and kept at all times below 5 KΩ. The 8 recording electrodes will be distributed across left and right hemi scalp positions (F3, F4, C3, C4, P3, P4, PO10, and PO9) according to the 10/20 EEG system, to capture among other sources, derived EEG activity associated to prefronto-central, and fronto-parietal motor/premotor networks. All EEG sessions will be conducted under the same conditions with a combined ground reference placed in the right earlobe. Ten minutes of resting-state EEG data (eyes open fixating on a target located at arm’s reach, ~ 57 cm) will be acquired during the baseline assessment, the post-stimulation regime assessment, and during the follow-up visit. EEG will be also continuously recorded during our visuo-motor adaptation task assessing cerebellar contributions to motor learning and during the AX-CPT paradigm assessing dorsolateral prefrontal contributions to sustained attention and cognitive control. Finally, 5 min of continuous resting-state EEG data (eyes open) will also be recorded prior to and following each of the 10 sessions of tDCS stimulation.

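### The EEG is cut into epochs before the 0.5–45 Hz forward-backward filter is applied, so each epoch carries edge distortion that reaches delta power and varies with an epoch length not yet chosen

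*Protocol article*

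**What the plan says.** The EEG data analysis section presents the preprocessing as an ordered sequence: "EEG data will be preprocessed using a hierarchically organized pipeline proceeding as follows". The first step is segmentation, with the epoch length still open: "Data will be first segmented into contiguous epochs after a preliminary investigation on which epoch length is the most robust for analyses". The filter is the second step, introduced by the word that fixes the order: "a 2nd-order infinite Butterworth forward and backward filter with a 0.5–45 Hz low-pass high-pass filter". Component-based artefact removal, rejection of epochs above 120 µV peak to peak and re-referencing follow.

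Band power is then computed for each electrode, with delta defined as 0.5–4 Hz, using "Welch’s method with a 500-ms periodogram". Both absolute and relative normalised power are taken. The Statistical analyses section compares band power by group and time, and relates EEG features to modelled electric field and to behaviour.

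The EEG acquisition section describes long uninterrupted recordings: "Ten minutes of resting-state EEG data" at each assessment, 5 minutes before and after every stimulation session, and continuous recording during both computer tasks.

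**The concern.** A recursive filter needs data before and after a point to give a correct value there. With a 0.5 Hz lower edge, one cycle lasts 1/0.5 = 2 s. When the filter is run forward and backward within a short segment, it has to invent what lies beyond each end, and the error is left inside the epoch. That error is slow, so it is counted largely as delta.

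Three things are at stake.

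- **Delta itself.** The Introduction links motor deficit to low-frequency increases in the injured hemisphere, and the study objectives seek neurophysiological normalisation and biomarkers. Delta is one of the EEG measures of most interest.
- **Relative power.** If delta is inflated, the relative power of the other bands falls even where their absolute power is unchanged.
- **The choice of epoch length.** It is to be settled by a preliminary look at robustness. Under the stated order, part of what differs between candidate lengths would be filter artefact.

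With about 15 patients per arm, measurement error that can be removed at no cost should be removed.

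**Working it through.** The plan gives no figure on this point to reproduce, so the check is a simulation.

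**Inputs from the protocol article**
- Sampling rate 500 Hz (EEG acquisition).
- 2nd-order Butterworth, 0.5–45 Hz, forward and backward, applied after segmentation (EEG data analysis).
- Welch spectrum with 500 ms windows and a Hanning taper; delta 0.5–4 Hz (EEG data analysis). A 500 ms window gives 1/0.5 = 2 Hz resolution, as the article states, so delta rests on the 2 Hz and 4 Hz bins.
- Record length 5 minutes, as in the per-session resting recordings (EEG acquisition).

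**Assumptions not in the article**
- Epoch length: 0.5 to 30 s.
- Background spectrum: 1/f or 1/f².
- Edge handling: short odd padding, no padding, or zero initial state.
- Removal or not of the mean in each Welch window.
- DC offset: 0 or 10 SD of the signal.

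**Settling time.** The filter's step transient takes about 1.0 s to spend 99% of its energy and 1.5 s to spend 99.9%. Epochs of 1–2 s or less are therefore of the same order as the transient.

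**Measure.** For epoch length L,

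R(L) = delta power (segment, then filter) / delta power (filter continuous record, then segment).

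Filtering the continuous record first is the reference, so R = 1.00 means no distortion.

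| Setting | 0.5 s | 1 s | 2 s | 4 s | 10 s |
|---|---|---|---|---|---|
| 1/f, padded, mean removed | 1.40 | 1.15 | 1.07 | 1.03 | 1.015 |
| 1/f, padded, mean not removed | 1.59 | 1.32 | 1.16 | 1.07 | 1.02 |
| 1/f, no padding, mean removed | 1.05 | 1.01 | 1.01 | 1.00 | 1.00 |
| 1/f, zero initial state, 10 SD offset | 8.7 | 2.8 | 1.75 | 1.33 | 1.17 |
| 1/f², padded, mean removed | 0.95 | 0.97 | 0.99 | 0.99 | 1.00 |
| 1/f², no padding, mean not removed | 0.75 | 0.87 | 0.95 | 0.98 | 0.99 |

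A further simulation of the 1/f padded case gave +44% to +69% at 0.5 s, +19% to +33% at 1 s, +7% to +17% at 2 s and +1% to +3% at 10 s. Together with the first two rows, this gives rounded ranges of +40% to +70%, +15% to +33%, +7% to +17%, and a few percent or less from 10 s.

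**Relative delta** in the first setting (1/f, padded, mean removed) is multiplied by 1.21, 1.09, 1.04, 1.02 and 1.01 at 0.5, 1, 2, 4 and 10 s.

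**Is the 500 ms window the cause?** No. With a Hann taper over the whole epoch instead (1/f, padded), R is 1.30 at 1 s, 1.15 at 2 s, 1.01 at 4 s and 1.00 at 10 s. The distortion remains at short epochs without the 500 ms window.

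**Reading.** In every setting the distortion fades as epochs lengthen. Epoch length is not the only driver: at 0.5 s, R runs from 0.75 to 8.7 depending on spectrum, padding and offset.

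**The case against.** **The effect is conditional.** A reader might infer that delta is always inflated, by an amount set by epoch length alone. The table does not support that. A 1/f² background gives a loss, unpadded filtering with mean removal leaves at most about 5% for a 1/f background, and a large uncorrected offset outweighs everything else. The settings that decide size and sign are implementation details that an article may leave to a fuller document, and their absence is no fault. This part of the objection stands. What remains is that the order of the two steps is written out, and that order is what allows the distortion.

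**Short epochs are not prescribed.** The length is open, and a robustness check might itself reveal length-dependent delta. That is fair: from 10 s the effect is a few percent or less unless a large offset is left in. But the stated order makes the check harder to read, and nothing in the article rules out short epochs.

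**No arm is favoured.** A reader might infer a biased group comparison. The same pipeline serves every group, task and visit, and the analyst is blinded. Nothing in the article points to differential error.

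**Patients may keep their ranking.** A reader might also infer that the artefact scrambles between-patient differences. In simulations with varied patient spectra, relative delta correlated with its correctly filtered value at 0.90–0.98 for 0.5 s epochs and at least 0.97 from 1 s. These values depend on the between-patient variation assumed, so no single correlation is a property of the pipeline. They do suggest that much of the distortion acts like a common scaling, and that the added noise is modest.

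**The outcomes are secondary.** EEG is secondary in a pilot trial, and the FMA-UE analysis does not depend on it. This stands and keeps the point minor.

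**Conclusion.** The point holds as a minor, avoidable defect. The stated order leaves edge distortion in each epoch that reaches the delta band. Its usual direction is upward: about +40% to +70% in absolute delta at 0.5 s, +15% to +33% at 1 s, +7% to +17% at 2 s, and a few percent or less from 10 s. Those figures assume a 1/f background and padded forward-backward filtering, neither of which the article specifies; a steep background can give little change or a small loss. Delta therefore depends in part on an epoch length still to be chosen.

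The consequence is distortion and some noise in secondary EEG outcomes: band power by group and time, and the correlations built on it. The effect on connectivity and entropy was not quantified. The documents do not support a claim of between-group bias or of any effect on the primary outcome.

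**What to change.** In the EEG data analysis section, reverse the first two steps. Apply the zero-phase Butterworth filter to the whole continuous recording, discard the first and last few seconds, then segment, run the independent component analysis and apply the 120 µV rejection. Choose the epoch length on data processed in that order, and fix it before the group comparisons.

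If the investigators already filter the continuous record first, correcting the text is enough. Otherwise the cost is one reordered sentence and reprocessing of stored recordings. No new data are needed, and losing a few seconds from a 5- or 10-minute resting record is immaterial.

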Over the last decade, classical non-invasive brain stimulation (NIBS) approaches with transcranial magnetic stimulation (TMS) or with tDCS have privileged clinical strategies based on either the upregulation of directly affected primary motor systems or the downregulation of homologue motor networks of the spared contralesional hemisphere linked with the former via inhibitory trans-callosal inter-hemispheric projections.

Nevertheless, the neural signature of MCA lesions has revealed strong interactions with alterations in sustained attention (engaging prefrontal and fronto-parietal systems) and large-scale desynchronization phenomena, both key factors limiting motor function or precluding recovery after brain damage [20–22]. More specifically, the severity of motor deficits has been associated with the strengthening of impaired inter-hemispheric functional connectivity between the dorsal attention network (DAN) and sensory-motor networks (SMN) [23–26] and high- and low-frequency oscillatory abnormalities (decreases and increases respectively) in the injured hemisphere [27, 28]. Likewise, a connectome-based predictive model exploring fractional anisotropy (FA) in stroke has highlighted the role of the ipsilesional dorsolateral prefrontal cortex (DLPFC) and cerebellar areas subtending motor symptoms and suggested their potential to convey motor recovery when manipulated with NIBS interventions [29]. In such a context conventional therapeutic neurostimulation directly modulating the excitability of damaged areas in charge of mapping lost functions has shown inconsistent outcomes. Heneforth, recent innovative approaches [30, 31] have been focused on reversing abnormal large-scale network signatures by inducing synergistic effects from spared cortical regions contributing to impaired function [30, 31].

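### Neither delta nor gamma power can be estimated as defined: the EEG is low-passed at 45 Hz but gamma runs to 60 Hz, and the 500-ms Welch window gives 2-Hz bins for a 0.5–4 Hz delta band

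*Protocol article*

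**What the plan says.** All of this is in the protocol article, mainly under EEG data analysis.

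- **Filter.** The pre-processing step is "a 2nd-order infinite Butterworth forward and backward filter", described as a "0.5–45 Hz low-pass high-pass filter at a resolution of 2 Hz (500 ms time windows"), "with a Hanning taper window will be applied".
- **Order of steps.** Spectral measures come after the filter: "Once data pre-processing is completed, (i) power spectrum density (PSD), (ii) connectivity, and (iii) complexity measures will be calculated".
- **Bands.** Power is computed for "δ: 0.5–4 Hz; θ: 4–8 Hz; α: 8–12 Hz; β: 12–30 Hz; γ: 30–60 Hz".
- **Estimator.** The spectrum is obtained "using Welch’s method with a 500-ms periodogram".

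EEG acquisition gives a 500-Hz sampling rate and ten minutes of resting-state recording at each assessment. Outcome measures lists EEG change as a secondary outcome. Statistical analyses compares power between groups band by band, and later correlates the EEG features that reach significance with the modelled electric field.

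**The concern.** Two pairs of figures in one section do not fit together, and no other section reconciles them. The gamma band extends 15 Hz past the low-pass cut-off, which is half of its 30-Hz width. The delta band starts at 0.5 Hz, but the stated resolution is 2 Hz, so no spectral bin lies between 0 and 2 Hz, and the next bin (4 Hz) is the edge shared with theta.

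These are the two ends of the spectrum. The Introduction motivates the work partly by "high- and low-frequency oscillatory abnormalities (decreases and increases respectively) in the injured hemisphere". If slow activity changes after stimulation, the plan as written could report it as delta or theta depending on where the 4-Hz bin is placed. A gamma result would describe a band other than the one named. Because every band is tested, and significant features go on to further correlations, a wrong label carries through to the mechanistic conclusions.

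**Working it through.** **Inputs from the article:** 500-Hz sampling; 2nd-order Butterworth, 0.5–45 Hz, forward and backward; Hanning taper; 500-ms Welch window; the five bands above. **Assumed, because not stated:** 50% window overlap; order 2 as the design order; segment mean either kept or removed (both shown); input spectrum between flat and 1/f².

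**1. Resolution.** 1/T = 1/0.5 s = 2 Hz, which reproduces the article's figure. The window holds 500 × 0.5 = 250 samples and the bins fall at 0, 2, 4, 6 … Hz. Delta contains 2 Hz only, plus 4 Hz if the shared edge is counted. The Hann noise bandwidth is 1.5/T = 3 Hz and its main lobe is 4/T = 8 Hz wide, against a delta band 3.5 Hz wide.

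**2. Where slow rhythms land.** Hann-tapered Welch was run on pure sinusoids. Entries are shares of the estimated power in the bins at 0 / 2 / 4 / 6 Hz.

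| Rhythm | Segment mean kept | Segment mean removed |
|---|---|---|
| 1 Hz | 0.48 / 0.50 / 0.02 / 0.00 | 0.12 / 0.80 / 0.08 / 0.00 |
| 3 Hz | 0.02 / 0.48 / 0.48 / 0.02 | 0.08 / 0.51 / 0.40 / 0.02 |
| 3.5 Hz | 0.00 / 0.31 / 0.62 / 0.07 | 0.02 / 0.35 / 0.57 / 0.06 |
| 5 Hz | 0.00 / 0.02 / 0.48 / 0.48 | 0.02 / 0.01 / 0.48 / 0.48 |

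- With the 4-Hz bin counted as theta, a 3-Hz rhythm puts 0.480 + 0.019 = 50% of its power in theta with the mean kept (41% with it removed). A 3.5-Hz rhythm puts 0.615 + 0.068 = 68% there (63% with the mean removed).
- With the 4-Hz bin counted as delta instead, the error reverses: a 5-Hz rhythm puts 0.019 + 0.480 = 50% in delta. Counting the bin in both bands counts that power twice.
- With the mean removed, only 25.2% of a 1-Hz rhythm's power survives, and 0.252 × 0.801 = 20% of the original reaches the 2-Hz bin.

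**3. What the filter leaves of gamma.** Power gain after a forward and backward pass is |H|⁴. For the low-pass edge alone this is [1/(1 + r⁴)]² with r = tan(πf/500)/tan(π·45/500).

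- 30 Hz: r = 0.657, gain 0.71
- 45 Hz: r = 1, gain 0.25
- 50 Hz: r = 1.118, gain 0.15
- 60 Hz: r = 1.363, gain 0.05

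The full 0.5–45 Hz band-pass gives 0.72, 0.25, 0.15 and 0.05. For a flat input, mean retention is 48% over 30–45 Hz and 13% over 45–60 Hz.

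| Input spectrum | Share of 30–60 Hz power above 45 Hz, before filter | After filter |
|---|---|---|
| Flat | 50% | 21% |
| 1/f² | 33% | 12% |

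If the stated order means a gentler first-order design, the after-filter share is about 20–33%.

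**4. What a longer window gives.** A 2-s window has 0.5-Hz spacing, the coarsest that places a bin on the lower delta edge. A 4-s window has 0.25-Hz spacing and (3.75 − 0.5)/0.25 + 1 = 14 delta bins. A rhythm centred on a bin then spreads only to its two neighbours (17% / 67% / 17%), so rhythms at 1, 3 and 3.5 Hz stay wholly in delta. At exactly 0.5 Hz about 17% still falls below the band. Ten minutes gives (600 − 4)/2 + 1 = 299 windows at 50% overlap, against (600 − 0.5)/0.25 + 1 = 2,399 with 500-ms windows.

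**The case against.** The strongest reply is that every arm and visit passes through the same filter and window, so comparisons between groups and over time remain like-for-like, and that EEG is a secondary outcome. Both parts stand. They limit the harm but do not make the band names correct.

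A second reply is that the article leaves epoch length to a preliminary investigation. That does not help, because the Welch window is fixed separately at 500 ms and a longer epoch does not sharpen its resolution. Nor is this detail left to another document: the article states the figures, and they conflict.

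Stronger readings are tempting, but the article does not support them:

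- A reader might infer that both ends of the spectrum are invalid, or that 45–60 Hz is removed. The roll-off is gradual: 45–60 Hz is strongly attenuated but present, and 30–45 Hz lies inside the nominal pass band. Delta survives as a coarse estimate around 2 Hz.
- A reader might infer that the biomarker and normalisation objectives rest on delta and gamma. The Introduction speaks only of high and low frequencies, Study objectives refers to synchronisation and abnormal neural states, and Statistical analyses tests all bands without ranking them.
- The 500-ms Welch window is stated for power only. It should not be read across to the coherence or entropy measures.
- Leakage of about 3 Hz is comparable to the width of delta, theta and alpha, but not of beta (18 Hz) or gamma (30 Hz).

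**Conclusion.** The point holds as an internal inconsistency that mislabels band power. The quantity called gamma would be mostly 30–45 Hz activity weighted by the filter slope, with about 12–21% from above 45 Hz under the order-2 design and an assumed 1/f² to flat input. Delta would rest on one interior bin. Depending on where the 4-Hz bin goes, about half the power of a 3-Hz rhythm is credited to theta, or about half of a 5-Hz rhythm to delta. If segment means are removed, about a fifth of a 1-Hz rhythm's power reaches delta.

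The leakage figures assume 50% overlap and pure sinusoids; real spectra are mixtures, so the figures show scale and do not predict a bias in the group contrasts. The FMA-UE primary analysis is unaffected. The plan should be corrected, because the delta, theta and gamma labels in the secondary EEG analyses cannot be defended as written.

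**What to change.** 1. **Gamma.** Define it as 30–45 Hz to match the filter, or raise the low-pass above 60 Hz and add a mains notch. Under the first option, state that power at the top of the band is still attenuated (25% kept at 45 Hz). Under the second, place the cut-off well above 60 Hz, since a filter run in both directions keeps only 25% of power at its own cut-off.
2. **Window.** Replace "with a 500-ms periodogram" with Welch windows of at least 2 s for resting-state power, for example 4-s Hann windows with 50% overlap, and say whether segment means are removed. State separately which window applies to the task recordings.
3. **Band edges.** Make adjacent bands half-open so that 4, 8, 12 and 30 Hz are each counted once.

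The cost is a change of script settings with no new data. Gamma is reported over a narrower band under the first option. Fewer windows are averaged per spectrum: up to 299 from ten minutes, before artefact rejection. Recruitment is planned to run to the end of 2025 and the analyst is to stay blind to the arm codes, so the settings can be fixed and recorded before unblinding.
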